for back or knee pain including number of sessions, and attended
orthopaedic consultation or received surgery.

See Table 2 for data collection time
points for secondary outcomes.

**Table 2 t02:** Secondary outcome measures.

**Construct**	**Measurement**	**Time-point (weeks)**
Disability and function	Trial one: Roland Morris Disability Questionnaire (RMDQ)^9^ Trial two: Western Ontario and McMaster Universities Osteoarthritis Index (WOMAC)^10^	0, 6, 26 0, 6, 26
Subjective weight	Self-reported weight (kg)	0, 6, 26
Objective weight	Measured to the nearest 0.1kg^11^	0^a^, 26
BMI	BMI calculated as weight/height squared (kg/m^2^)^12^	0, 6, 26
Waist circumference	Measured to the nearest 0.1cm^11^	26
Quality of life	Short Form Health Survey version 2 (SF12.v2)^7^	0, 6, 26
Perceived change in condition	Global Perceived Effect scale (–5 to 5 scale)^13^	6, 26
Emotional distress	Depression Anxiety Stress Scale-21 (DASS-21)^14^	0, 26
Sleep quality	Item 6 from the Pittsburgh Sleep Quality Index^15^	0, 6, 26
Physical activity	The Active Australia Survey^16^	0, 6, 26
Diet	Short food frequency questionnaire^17^	0, 6, 26
Alcohol consumption	Alcohol Use Disorders Identification Test (AUDIT)^18^	0, 6, 26
Smoking prevalence	Self-reported current smoking status^19^	0, 6, 26
Pain Attitudes	Survey of Pain Attitudes (SOPA)^20^	0, 6, 26
Fear avoidance beliefs	Fear Avoidance Beliefs Questionnaire (FABQ)^21^	0, 26
Health care utilisation	Medication use for back (trial one) or knee pain (trial two) Visits for back (trial one) or knee pain (trial two) – type and number of sessions Attended orthopaedic consultation, received surgery	0, 6, 26 0, 6, 26 26

a Intervention group of low back pain patients (trial one) only.
BMI: Body Mass Index.

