#### Sample size

The sample size for both trials was calculated using Stata sample size
calculator.

For trial one a standard deviation of 2.3, a two-sided alpha of 0.025 (to
account for two outcomes of interest, the primary outcome (pain) and the key
secondary outcome (weight)^22^ and allowing for 15% loss to follow-up was used. A sample size of 80
participants per group (n=160) has 90% power to detect a clinically
meaningful difference of 1.5 points in pain intensity (pain NRS) between
intervention and control groups^23^. This sample also provides power 80% to detect a 6% reduction in
weight in the underlying sampling population, based on evidence from other
musculoskeletal conditions this is hypothesised to lead to a clinically
meaningful reduction in pain^23^.

For trial two a standard deviation of 2.7, a two-sided alpha of 0.025 (to
account for two outcomes of interest, the primary outcome (pain) and the key
secondary outcome (weight)^22^ and allowing for 15% loss to follow up, a sample of 60 participants
per group will provide 90% power to detect a clinically meaningful
difference of 2 points in pain intensity (pain NRS) scores between
intervention and control groups at 26 weeks. This sample also provides 80%
power to detect a 6% weight reduction which is hypothesised to be lead to a
clinically meaningful reduction in pain^23^.

In these calculations the increase in statistical power conferred by reducing
error variance through repeated outcome measures over time and the
correlations among repeated measures have been conservatively ignored.

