### Analysis principles

Primary analyses will be conducted independently by an independent statistician
who is blinded to group status.

Analyses will be conducted using SAS V9.4 (SAS Institute, Cary, North Carolina,
USA). Intention-to-treat (ITT) (analysed as randomised) will be utilised. All
statistical tests will be two-tailed. Treatment effect for the primary and
secondary outcomes will be considered significant if *p*≤0.025
and *p*≤0.01, respectively.

Summaries of continuous variables that are symmetrically distributed will be
presented as means and standard deviations (SD) or medians and inter-quartiles
for skewed data, whereas categorical variables will be presented as frequencies
and percentages. Large count variables will be reported as medians and
interquartile ranges, low counts (max count <5) will be presented as
frequencies and percentages.

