### Secondary analysis

Between group differences in the trajectory of pain intensities over the
follow-up period will be examined using growth curve modelling. Hierarchical
linear models will be used, with fixed effects for treatment group, time, and
the interaction between the two. The model will include random subject-level
intercepts and slopes. A linear growth trend will initially be assumed, and if
not appropriate different functional forms for the trend will be applied (for
example the square root transformation). If an appropriate functional form
cannot be determined a flexible piecewise linear model will be used^26^. We will also investigate treatment effect heterogeneity that may exist
in latent subgroups of participants through growth mixture models^27^. In these models a number of latent classes are specified that model the
potential for participants to have different trajectory types, the functional
forms identified from the previous growth curve analyses will inform the
functional forms for this analysis. The model will include the following random
effects that are all conditional trajectory class membership: intercept linear
slope and quadratic slope. The random effects are influenced by the treatment
group, so there will potentially be 3 lots of treatment effects (for each random
effect) for each latent class.

Longitudinal generalised linear mixed models will be used to assess treatment
effect on post randomisation secondary outcome measurements with random
intercepts for individuals to account for correlation of repeated measures and
an appropriate link function dependent on the type and distribution of the data.
We will compare the adjusted mean change (continuous variables) or relative
risks (dichotomous variables) in outcome from baseline to each time point
between the treatment and control groups. A binomial distribution family (with
log link) will be used for dichotomous outcomes (sleep quality, smoking
prevalence), and a Poisson or negative-binomial distribution family (with a log
link function) will be used for count outcomes (health care utilisation) based
on assessment of data dispersion. T-tests will be used to test between group
differences in variables collected only at 26 weeks (objective weight, BMI,
waist circumference). See Table 4 for
details.

**Table 4 t04:** Secondary outcomes.

**Outcome**	**Intervention**	**Control**	**Intervention - control**
Disability and function (Trial 1: RMDQ / Trial 2: WOMAC)			

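### Random intercepts alone force one variance on the week-6 and week-26 change; if weight change spreads out over time, the week-26 standard error for self-reported weight is too small

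*Protocol article*

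**What the plan says.** In the Secondary analysis section of the protocol article, generalised linear mixed models assess the treatment "effect on post randomisation secondary outcome measurements with random" "intercepts for individuals to account for correlation of repeated measures". No random slope, visit-specific variance, unstructured covariance or robust standard error is mentioned for these outcomes. The contrast follows: "We will compare the adjusted mean change (continuous variables) or relative" risks, from baseline to each visit. For the pain trajectory the same section is more flexible: "The model will include random subject-level" intercepts and slopes.

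Table 2 puts "Self-reported weight (kg)" at weeks 0, 6 and 26. Objective weight has a baseline only in the trial-one intervention group, and the text gives it and waist circumference a t-test at week 26. The text also counts BMI among the variables collected only at week 26, whereas Tables 2 and 4 show it at weeks 0, 6 and 26.

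Analysis principles says that "statistical tests will be two-tailed" and sets the threshold for secondary outcomes ("and *p*≤0.01, respectively"). Sample size lowers alpha to "account for two outcomes of interest, the primary outcome (pain) and the key" secondary outcome, weight, without saying which weight measure is meant.

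**The concern.** A random intercept with a single residual variance is compound symmetry: every visit has the same variance and every pair of visits the same correlation. Any two changes then have the same variance, so the model gives the 6-week and the 26-week change the same standard error (complete data). Under a six-month coaching programme some participants may lose weight steadily while others stay level or gain. If so, change at week 26 varies more than change at week 6, and the pooled standard error is too small at week 26 and too large at week 6.

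Self-reported weight is the only weight measure with a baseline in both arms, so it is the only one on which change can be compared, and it goes through this model. At stake are the size of its week-26 test and the coverage of its week-26 confidence interval in Table 4.

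**Working it through.** **Inputs from the article:** visits 0, 6 and 26; random intercept; contrast on change from baseline; two-sided 0.01; 68 per arm (80 less 15% loss) in trial one and 51 (60 less 15%) in trial two.

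**Assumed, because the article gives no figure:** SD of weight change 1.5-3 kg at week 6 and 4-6 kg at week 26, correlation between the two changes 0.4-0.6.

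**Formulas.** Let a and b be the true variances of change at weeks 6 and 26, and c their covariance.

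- *Baseline as a response row.* The model gives every change the mean of the three pairwise difference variances (0-6, 0-26, 6-26): [a + b + (a + b − 2c)]/3 = 2(a + b − c)/3.
- *Baseline as a covariate* (slope on baseline taken as near 1). The model pools the variance over two visits: (a + b)/2.
- Week-26 SE ratio = √(model variance / b). Actual level = 2[1 − Φ(2.576 × ratio)]. 95% interval coverage = 2Φ(1.96 × ratio) − 1.

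The article does not say how baseline enters, so both versions are shown. The ratio does not depend on sample size.

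**The plan's own figure first.** If a = b and c = a/2 (compound symmetry), the first formula gives 2(1.5a)/3 = a. The ratio is 1.00 and the level 1.0%. Simulation of 20,000 trials gave 0.9-1.0%. The stated 0.01 holds when the model is true.

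**Worked example.** SDs 2 and 5 kg, correlation 0.5: a = 4, b = 25, c = 0.5 × 2 × 5 = 5.

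- Baseline as response: 2 × 24/3 = 16. Week 26: √(16/25) = 0.80, level 3.9%, coverage 88%. Week 6: √(16/4) = 2.0, so the SE is doubled.
- Baseline as covariate: 29/2 = 14.5. Week 26: √(14.5/25) = 0.76, level 5.0%.

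**Over the assumed range, week 26:**

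| Baseline handled as | SE ratio | Level at nominal 1% | 95% coverage |
|---|---|---|---|
| Response row | 0.78-0.92 | 1.8-4.5% | 87-93% |
| Covariate | 0.73-0.88 | 2.3-6.0% | 85-92% |

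The week-26 SE is therefore 8-27% too small. The week-6 SE is 1.15 to 3.2 times too large.

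**Reporting error.** Independent error with SD e in each self-report adds 2e² to a and b and e² to c. Worked example, baseline as response:

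| e (kg, assumed) | a, b, c | Model variance | Ratio | Level |
|---|---|---|---|---|
| 0 | 4, 25, 5 | 16 | 0.80 | 3.9% |
| 1 | 6, 27, 6 | 18 | 0.82 | 3.5% |
| 2 | 12, 33, 9 | 24 | 0.85 | 2.8% |
| 3 | 22, 43, 14 | 34 | 0.89 | 2.2% |

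**Questionnaire outcomes.** Assumed correlations 0.7/0.6/0.65 (0-6, 0-26, 6-26) give difference variances 0.6, 0.8 and 0.7 (in units of the visit variance), mean 0.7; the ratio is √(0.7/0.8) = 0.94. Correlations 0.6/0.5/0.6 give 0.93. Simulated levels were 1.5-1.6%.

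**After the fix.** With week-specific variances the simulated level was 0.8-1.1% in every scenario, with 68 or 51 per arm.

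**The case against.** The strongest objection is that the figures come from outside the article. It gives no SD or correlation for weight change, and every assumed week-6 SD lies below every assumed week-26 SD, so that range cannot return a null result. This stands: the size is conditional, and with equal change variances and compound symmetry there is no error.

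A reader might infer that the key secondary test fails. The documents do not support that, because Sample size does not say which weight measure is meant, and measured weight is t-tested at week 26, where the problem cannot arise.

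A reader might also extend the point to every repeated secondary outcome. That is too broad. DASS-21 and FABQ have only weeks 0 and 26, so with complete data one change is modelled and nothing is pooled. The global perceived effect scale has no baseline. No calculation here covers the binary or count outcomes, so it gives no ground for robust standard errors there.

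Nor does it follow that an early weight effect would usually be missed. In the worked example with 68 per arm, power for a 1.5 kg week-6 difference falls from 96% to 22%, but for 2.5 kg it stays at 71-100% over the whole assumed range. The conclusion depends on the effect chosen.

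Two smaller objections have some weight. Random slopes for pain serve a trajectory question with eight measurements, so they do not show that the authors expected weight to diverge. A condensed article may also omit the residual covariance and the standard-error method. Still, the article does name its device for within-person correlation, and the device it names is restrictive.

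**Conclusion.** The point holds in conditional form. As written, the model imposes equal variance on the week-6 and week-26 change, and the article offers no justification for that. If weight change spreads out over time within the assumed range, the week-26 standard error for self-reported weight is about 8-27% too small and the nominal 0.01 test runs at about 2-6%. Reporting error puts the likely value towards the lower end. BMI shares the problem only if it is modelled at weeks 0, 6 and 26. For questionnaire outcomes the effect is minor. Objective weight, waist circumference and the primary AUC comparison are untouched.

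The figures should not be read as the known error rate of this trial. They show what the stated model would do under a plausible but assumed pattern of weight change. The case for changing the model rests on the fact that the alternative is valid whether or not compound symmetry holds.

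**What to change.** For continuous secondary outcomes measured at weeks 0, 6 and 26, replace the random intercept by an unstructured covariance over visits, with a small-sample degrees-of-freedom method such as Kenward-Roger. State whether baseline is a response or a covariate, and whether BMI goes through this model or the t-test.

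The cost is one sentence in the plan and one line of SAS code. The unstructured matrix has six parameters for three visits, or three for two visits, against two for the random-intercept model. If weight change does spread out, the week-26 interval for weight becomes wider. The models for binary and count outcomes need no change on this account.

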#### Secondary outcomes

The secondary outcomes include:

•Physical disability and function, measured in trial one using the
Roland Morris Disability Questionnaire (RMDQ)^9^ 0-24 scale and measured in trial two using the Western
Ontario and McMaster Universities Osteoarthritis Index (WOMAC) 0-96
scale^10^;•Self-reported weight (kg);•Objective weight (kg) measured to the nearest 0.1kg by a trained
research assistant using International Society for the Advancement
of Kinanthropometry (ISAK) procedures^11^;•BMI calculated as weight /height squared (kg/m^2^)^12^;•Waist circumference measured by a trained research assistant using
ISAK procedures taken at the level of the narrowest point between
the inferior rib border and the iliac crest using a flexible tape
measure to the nearest 0.1 cm^11^;•Quality of life, measured using the physical and mental health
component scores from the 12-item Short Form Health Survey version 2
(SF12.v2)^7^;•Global perceived change in symptoms, measured using the Global
Perceived Effect (GPE) scale (-5 ‘vastly worse’ to 5 ‘completely
recovered’)^13^;•Emotional distress, measured using the Depression Anxiety Stress
Scale-21 (DASS-21) 0-63 scale^14^;•Sleep quality, measured using item 6 from the Pittsburgh Sleep
Quality Index (response options: very bad, fairly bad, fairly good,
very good)^15^;•Physical activity, measured using the Active Australia Survey^16^, reported as the average minutes spent participating in
moderate-to-vigorous physical activity (MVPA) per week;•Diet, measured using a short food frequency questionnaire (FFQ)^17^, reported as serves of fruit (0-1, 2 or more), serves of
vegetables (0-2, 3-4, 5 or more), serves of discretionary foods
including processed meats, salty snacks, takeaway meals, sweet or
savoury snacks, confectionary and sugar sweetened beverages (more
than once per week, once per week or less);•Alcohol consumption measured using the Alcohol Use Disorders
Identification Test (AUDIT) 0-12 scale^18^;•Smoking prevalence (have you smoked any tobacco in the last 4 weeks?
(this can include cigarettes, roll your own, pipes, cigars or any
other tobacco products))^19^;•Attitudes and beliefs, measured using the Survey of Pain Attitudes
(SOPA)^20^; and the physical component of the Fear Avoidance Beliefs
Questionnaire (FABQ) 0-24 scale^21^; and•Health care utilisation for each trial respectively, including back
or knee pain medication use (name), type of health service utilised

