Week 26	mean (SD)	mean (SD)	mean (95% CI)
Overall	mean (SD)	mean (SD)	mean (95% CI)
Smoking prevalence			
Baseline	n/N (%)	n/N (%)	OR (95% CI)
Week 6	n/N (%)	n/N (%)	OR (95% CI)
Week 26	n/N (%)	n/N (%)	OR (95% CI)
Overall	n/N (%)	n/N (%)	OR (95% CI)
Pain Attitudes (SOPA)			
Baseline	mean (SD)	mean (SD)	mean (95% CI)
Week 6	mean (SD)	mean (SD)	mean (95% CI)
Week 26	mean (SD)	mean (SD)	mean (95% CI)
Overall	mean (SD)	mean (SD)	mean (95% CI)
Fear avoidance beliefs (FABQ)			
Baseline	mean (SD)	mean (SD)	mean (95% CI)
Week 26	mean (SD)	mean (SD)	mean (95% CI)
Overall	mean (SD)	mean (SD)	mean (95% CI)
Health care utilisation (Medication use for back or knee pain)			
Baseline	n/N (%)	n/N (%)	OR (95% CI)
Week 6	n/N (%)	n/N (%)	OR (95% CI)
Week 26	n/N (%)	n/N (%)	OR (95% CI)
Overall	n/N (%)	n/N (%)	OR (95% CI)
Health care utilisation (Visits for back or knee pain)			
Baseline	n/N (%)	n/N (%)	OR (95% CI)
Week 6	n/N (%)	n/N (%)	OR (95% CI)
Week 26	n/N (%)	n/N (%)	OR (95% CI)
Overall	n/N (%)	n/N (%)	OR (95% CI)
Health care utilisation (Attended orthopaedic consultation for back or knee)			
Week 26	n/N (%)	n/N (%)	OR (95% CI)
Health care utilisation (Received surgery for back or knee)			
Week 26	n/N (%)	n/N (%)	OR (95% CI)

a Intervention group of low back pain patients (trial one) only.

RMDQ=Roland Morris Disability Questionnaire; WOMAC=Western Ontario
and McMaster Universities Index; BMI=Body Mass Index; SF12.v2=Short
Form Health Survey version 2; PCS=Physical Component Score;
MCS=Mental Component Score; GPE=Global Perceived Effect;
DASS-21=Depression Anxiety Stress Scale; MVPA=Moderate-to-Vigorous
Physical Activity; AUDIT=Alcohol Use Disorders Identification Test;
SOPA=Survey of Pain Attitudes; FABQ=Fear Avoidance Beliefs
Questionnaire.

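### Health care utilisation is assigned as a whole to a count model, although Table 4 reports medication use, orthopaedic consultation and surgery as yes/no items; their confidence intervals may be too wide, by an amount that depends on prevalence

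*Protocol article*

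**What the plan says.** The Secondary analysis section sets out generalised linear mixed models for the secondary outcomes, with a random intercept per participant and "an appropriate link function dependent on the type and distribution of the data". It then names families by outcome.

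- **Binomial family:** "log link) will be used for dichotomous outcomes (sleep quality, smoking" prevalence). No health-care item is named here.
- **Poisson or negative-binomial family:** "link function) will be used for count outcomes (health care utilisation) based" on data dispersion. The domain is not divided.
- **Effect measure for dichotomous outcomes:** relative "risks (dichotomous variables) in outcome from baseline to each time point".

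The Secondary outcomes section shows that the domain is mixed. It covers back "or knee pain medication use (name), type of health service utilised" with the number of sessions, and whether the participant attended an "orthopaedic consultation or received surgery". In Table 2, medication and visits are collected at weeks 0, 6 and 26, and consultation and surgery at week 26 only.

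Table 4 has rows such as "Health care utilisation (Medication use for back or knee pain") and "Health care utilisation (Attended orthopaedic consultation for back or knee"). Every health-care row, including surgery and visits, is laid out as n/N (%) per arm with an OR (95% CI), exactly as for sleep quality and smoking.

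**The concern.** The text and the results table treat the same items as different kinds of data. Attending a consultation and receiving surgery are 0/1 per person, and Table 4 treats medication use the same way. A Poisson model takes the variance of a 0/1 variable to be its mean p, when it is p(1-p), so the model-based standard error is too large. The dispersion check cannot repair this. It chooses between Poisson and negative binomial, and the negative binomial can only add variance, whereas 0/1 data have less variance than Poisson.

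The effect measures do not fit either. A log-link count model gives a rate ratio, the text promises relative risks for dichotomous outcomes, and Table 4 prints odds ratios.

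Change in health care and medication use is among the secondary aims in the Objectives section. An inflated standard error pushes these results towards an uninformative finding of no difference.

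**Working it through.** The article states no prevalence, target effect or power for any health-care item, so there is no figure of the plan's own to reproduce. The check asks how far the assigned model misstates the standard error, and what that does to the test.

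**Inputs from the article**
- Secondary outcomes are tested two-sided at p≤0.01 (Analysis principles), so the critical value is 2.576.
- Sample size section: 80 per arm in trial one and 60 in trial two, with 15% loss. This leaves 80 × 0.85 = 68 and 60 × 0.85 = 51.
- No robust variance or scale correction is mentioned.

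**Assumed:** all prevalences, and the within-person correlation used in step 4.

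**1. Standard error of the log relative risk at one time point, n per arm**
- Binomial, log link: sqrt((1-p1)/(n·p1) + (1-p2)/(n·p2))
- Poisson, model-based: sqrt(1/(n·p1) + 1/(n·p2))

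With equal prevalence p in both arms, the ratio of Poisson to binomial is 1/sqrt(1-p). The last column is 2·(1 - Φ(2.576/sqrt(1-p))).

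| p | SE ratio | True type I error at nominal 0.01 |
|---|---|---|
| 5% | 1.03 | 0.008 |
| 10% | 1.05 | 0.007 |
| 30% | 1.20 | 0.002 |
| 50% | 1.41 | 0.0003 |
| 70% | 1.83 | below 0.0001 |

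**2. Worked example, 80% versus 60%, n = 68**
- Events expected: 54.4 and 40.8.
- Binomial SE = sqrt(0.2/54.4 + 0.4/40.8) = 0.116.
- Poisson SE = sqrt(1/54.4 + 1/40.8) = 0.207.
- log(0.8/0.6) = 0.288.
- Power with the binomial SE: Φ((0.288 - 2.576 × 0.116)/0.116), about 46%.
- Power with the Poisson SE (the estimate still varies with the binomial SE): Φ((0.288 - 2.576 × 0.207)/0.116), about 2%.

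**3. Other assumed cases**, from simulation with 200,000 draws each. Each cell gives power with the Poisson model-based SE, then with the binomial SE.

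| Prevalences | 68 per arm | 51 per arm |
|---|---|---|
| 80% vs 60% | 1.4% / 46% | 0.6% / 32% |
| 80% vs 40% | 75% / 99% | 49% / 94% |
| 70% vs 50% | 4% / 39% | 2% / 26% |
| 70% vs 30% | 85% / 99% | 64% / 93% |
| 50% vs 25% | 37% / 63% | 21% / 46% |
| 30% vs 10% | 45% / 57% | 23% / 34% |

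A Poisson model with robust (sandwich) standard errors gives the binomial column at a single time point.

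**4. Overall estimate across weeks 6 and 26.** If the random-intercept variance is estimated near zero, the ratio becomes about 1/sqrt((1-p)(1+ρ)), where ρ is the within-person correlation. At p = 0.7 and ρ = 0.6 this is 1/sqrt(0.3 × 1.6) = 1.44, against 1.83 at one time point.

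**The case against.** The best defence is that the section works by data type and the bracketed outcomes are only examples. The binomial bracket is plainly incomplete: fruit and discretionary foods have two categories each and appear in Table 4 with odds ratios, yet they are not named there. The section also refers the reader to Table 4, which treats the health-care items as proportions. On this view the fault is loose wording. The first part stands: absence from the binomial bracket proves nothing. But the count sentence does not merely omit these items. It names their domain as the count outcome, and the clause on choosing by data type concerns the link function.

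A second defence is that medication use may be a count. Medications are recorded by name and coded by class (Concomitant treatments), and Analysis principles presents low counts as frequencies and percentages. This is fair, and the point applies to medication only if it is analysed as yes/no. It would explain the n/N (%) but not the odds ratio, and it does not reach consultation or surgery.

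A third is that a condensed article may leave out a robust variance. That is possible. Had one been intended, the excess at a single time point would vanish, but the mismatch of data type and effect measure would remain.

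A reader might go further and infer that a real fall in medication use would almost never be detected. The article does not support that. It requires a high prevalence, a moderate change and no robust variance, none of which is given. Under the same Poisson standard error with 68 per arm, power is 75% for 80% versus 40% and 45% for 30% versus 10%. Nor are all the intervals materially too wide: patients booked for surgery in the next 6 months are excluded, so surgery may be rare, and at 5-10% the excess is only 3-5%.

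**Conclusion.** The point holds in a limited form. The Secondary analysis text assigns the whole domain to count models, Table 4 reports it as proportions with odds ratios, and only the number of sessions is clearly a count. Followed literally with model-based standard errors, the plan gives intervals for the yes/no items that are too wide by about 1/sqrt(1-p) at one time point. That is negligible for rare items, considerable for common ones, and smaller for the overall estimate when visits are correlated.

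The error is conservative: type I error falls below the nominal level, so no false claim of benefit follows. The cost is lost power on a stated secondary aim. Its size cannot be fixed from the article, because it depends on unstated prevalences and effects. Even with the right standard error, several of the assumed cases have power below 50% at p≤0.01, so the correction restores honest intervals rather than adequate power. That consultation and surgery have only one measurement, leaving a random intercept nothing to work on, is a minor addition; the article does not say explicitly that they would be given one.

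**What to change.** In the Secondary analysis section:

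1. List attended consultation and received surgery with the dichotomous outcomes, and medication use too if it is analysed as yes/no. Use the binomial family, or Poisson with robust standard errors if the log-binomial model does not converge. If medication use is to be a count of medications, say so.
2. Keep the Poisson or negative-binomial model, with its dispersion check, for the number of sessions.
3. Compare consultation and surgery, collected only at week 26, with a single-time-point binary method.
4. Make Table 4 match: one effect measure for the yes/no items, in agreement with the text, and a count summary with a rate ratio for sessions, whose row now shows n/N (%) and an OR.

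The cost is a sentence or two of wording and some table headings, with no new data. The practical risk is non-convergence of the log-binomial model for common items, which the stated fallback covers. As the plan was signed before analysis, the change should be recorded as a dated clarification.

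### BMI is given a 26-week t-test as if it had no earlier values, against Tables 2 and 4; the t-tests for objective weight and waist are valid but leave baseline weight and BMI unused

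*Protocol article*

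**What the plan says.** The Secondary analysis section describes two routes for secondary outcomes. Repeated outcomes go to longitudinal mixed models that compare adjusted change from baseline between the arms. The other route is: "T-tests will be used to test between group differences in variables collected only at 26 weeks (objective weight, BMI, waist circumference").

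Table 2 gives these measurements and time points in weeks:

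- BMI: "BMI calculated as weight/height squared (kg/m^2^)^12^ 0, 6, 26"
- Self-reported weight: "Self-reported weight (kg) 0, 6, 26"
- Objective weight: "Measured to the nearest 0.1kg^11^ 0^a^, 26", where footnote a reads "Intervention group of low back pain patients (trial one) only"
- Waist: "Measured to the nearest 0.1cm^11^ 26"

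Table 4 has BMI rows for baseline, week 6, week 26 and overall, each with a between-group difference. For objective weight it marks the control baseline and the baseline difference as not applicable, and gives a difference at week 26 only. Waist has a week 26 row only.

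The Sample size section calls weight the key secondary outcome, without saying whether it is measured or self-reported. For trial one it claims "power 80% to detect a 6% reduction in" weight, and it makes the same claim for trial two.

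**The concern.** BMI has two pre-specified analyses that cannot both be carried out. The text treats it as a single late measurement, while the tables treat it as a repeated outcome with a baseline. An analyst following the text would discard the baseline and the week 6 value and could not complete Table 4.

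For objective weight and waist the question is efficiency. Body size varies widely between people, and much of that variation is already present at baseline. A t-test on 26-week values puts all of it into the error term. Self-reported weight and BMI are recorded at baseline in both arms and would be expected to explain a good part of it. The Sensitivity analyses section already uses baseline BMI as a covariate for pain, but the plan names no baseline covariate for measured weight or waist.

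**Working it through.** **Step 1. Text against tables**

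| Variable | Time points (Tables 2 and 4) | Text rule | Consistent? |
|---|---|---|---|
| BMI | 0, 6, 26 | 26-week t-test | No |
| Objective weight | 26; week 0 in the trial one intervention arm only | 26-week t-test | Yes for a between-arm comparison |
| Waist | 26 | 26-week t-test | Yes |
| Self-reported weight | 0, 6, 26 | Not in the t-test list, so mixed model | Yes |

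**Step 2. The plan's own power figure**

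The 80% power for a 6% weight reduction cannot be reproduced, because the article gives no SD, mean or baseline correlation for weight. It can be inverted.

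- Completers after 15% loss: 80 × 0.85 = 68 per arm (trial one); 60 × 0.85 = 51 per arm (trial two).
- For an unadjusted two-sample t-test at two-sided alpha 0.025 (noncentral t), 80% power needs a standardised difference of 0.534 (trial one) or 0.618 (trial two).
- The SD this implies is 6%/0.534 = 11.2% of mean weight in trial one and 6%/0.618 = 9.7% in trial two.

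The stated power is therefore attainable without adjustment only if the between-person SD is no larger than these values.

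**Step 3. Variance saved by adjustment**

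Residual SD = SD × √(1 − r²), where r is the correlation between the baseline covariate and the 26-week outcome. The factor 1 − r² is 0.51 at r = 0.7, 0.36 at r = 0.8 and 0.19 at r = 0.9. This holds whatever the SD.

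**Step 4. Power for a 6% difference in weight**

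Assumptions that are not in the article: SD 12% to 18% of mean weight, and r from 0.7 to 0.9.

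- Standardised difference d = 6/(SD% × √(1 − r²)).
- Noncentrality = d × √(n/2), with 2n − 2 degrees of freedom. The one degree of freedom spent on the covariate is ignored.
- Example, trial one, SD 12%, no adjustment: d = 6/12 = 0.50; noncentrality = 0.50 × √34 = 2.92; critical value 2.27; power 74%.

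Each cell gives power at SD 12%, then at SD 18%, with alpha 0.025:

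| Analysis | Trial one (68 per arm) | Trial two (51 per arm) |
|---|---|---|
| t-test, no covariate | 74% to 38% | 60% to 28% |
| Adjusted, r = 0.7 | 96% to 68% | 89% to 53% |
| Adjusted, r = 0.8 | 99% to 83% | 97% to 70% |
| Adjusted, r = 0.9 | at least 98% | at least 94% |

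The table uses 0.025 because weight was sized at that level. The Analysis principles section sets 0.01 for secondary outcomes. At 0.01 the unadjusted figures are 62% to 26% and 46% to 18%, and at r = 0.8 they are 99% to 73% and 94% to 57%.

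**The case against.** Several points on the other side stand.

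- **Validity.** In a randomised comparison an unadjusted t-test is valid, and its error rate already allows for chance imbalance. The plan openly takes the same unadjusted approach to its primary outcome. For objective weight and waist, adjustment is an improvement and not the correction of an error.
- **The tables.** A reader might infer that all three t-tests contradict Tables 2 and 4. Only the one for BMI does. Waist has no baseline, and the single-arm baseline of objective weight cannot support a between-arm comparison of change.
- **The key secondary outcome.** A reader might infer that the plan wastes most of its power for that outcome. The documents do not support this. Weight is not identified as the measured one, and self-reported weight goes to the mixed model, which uses change from baseline. The loss also depends on an SD and a correlation that the article does not give. If the SD is near 11.2% (trial one) or 9.7% (trial two), the t-test keeps the stated 80% at alpha 0.025.
- **Range for BMI.** Entry is limited to BMI 27 to below 40, so the 12–18% range assumed for weight should not be carried over to BMI.
- **Missing values.** The article does not say that the t-tests use only those measured at week 26, so no finding is made on that.

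One defence does not stand: that BMI in the t-test list means a separate BMI from measured weight. The outcome list and Table 2 define a single BMI variable, and the text does not distinguish two.

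**Conclusion.** The rule for BMI is wrong as written and has to be reconciled with Tables 2 and 4. This conclusion needs no assumption.

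For objective weight and waist the t-tests are valid but leave usable baseline information aside. The cost is precision, not bias. Adjustment reduces residual variance by the factor 1 − r². How much power that buys is unknown. The gains in the working, for example from 60–28% to 97–70% in trial two at r = 0.8, hold only for measured weight under the assumed SD of 12–18% and the assumed r. How far this bears on the key secondary outcome depends on which weight measure is meant, and the article leaves that open.

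Severity: should fix.

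**What to change.** 1. Remove BMI from the t-test list and analyse it in the longitudinal mixed model with its baseline. Compute it from self-reported weight at weeks 0, 6 and 26, and report any 26-week BMI from measured weight separately, so that change over time does not mix two methods.
2. Analyse 26-week objective weight and waist by linear regression on arm plus baseline self-reported weight or BMI. Name the covariate in advance.
3. State whether the key secondary outcome is measured or self-reported weight, and at which significance level it is tested: 0.025 as in Sample size, or 0.01 as in Analysis principles.

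The cost is a few sentences in the analysis plan, written before the data are analysed. The covariates are already in the data collection schedule, so no new data are needed.
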